## **14 Study Finances**

### ***14.1 Funding Source***

This study is funded by the NIH

### ***14.2 Conflicts of Interest***

Any investigator who has a conflict of interest with this study (patent ownership, royalties, or financial gain greater than the minimum allowable by their institution, etc.) will have the conflict reviewed by a properly constituted Conflict of Interest Committee with a Committee-sanctioned conflict management plan that has been reviewed and approved by the study sponsor prior to participation in this study. All University of California investigators will follow the University conflict of interest policy.

### ***14.3 Subject Stipends or Payments***

Caregivers will not receive any study stipends or payments.

#### ***Costs Covered by Study:***

Once determined eligible and the pet is enrolled, the study will cover the cost of appointment fees, blood sampling, sedation, thoracic radiographs, single dose of doxorubicin + administration, and study related IL-15, PPE, and procedures. The study will provide the use of the nebulizer, however, this will need to be returned at the end of the treatment. Study will also cover costs of screening echocardiogram and MDR testing in at-risk breeds.

#### ***Costs NOT Covered by Study:***

Owners are responsible for eligibility/screening which includes initial or recheck office examination, bloodwork including CBC/Chemistry panel, urinalysis, thoracic radiographs, and confirmed diagnosis of osteosarcoma or melanoma. Additional diagnostics may be recommended based on clinician preference and would be at the owner's expense.

If the pet experiences an adverse event(s) as a result of taking part in this study, and is in need of medical treatment, the study sponsors will offer to pay for medical treatment for injury/side effects up to \$2000. The study can ONLY pay for costs of therapy incurred at the UC Davis Veterinary Medical Teaching Hospital. Costs associated with treatment beyond \$2000 will be at the expense of the owner.

## **15 Publication Plan**

Neither the complete nor any part of the results of the study carried out under this protocol, nor any of the information provided by the sponsor for the purposes of performing the study, will be published or passed on to any third party without the consent of the principal investigator. Any investigator or research assistant involved with this study is obligated to provide the principal investigator with complete test results and all data derived from the study.

CONFIDENTIAL

This material is the property of the University of California. Do not disclose or use except as authorized in writing by the study sponsor.

## 16 Veterinary Center for Clinical Trials Standard Operating Procedures

This study is subject to the following VCCT SOPs, which will be reviewed with study personnel involved in relevant study procedures and logged per VCCT policy.

### 16.1 Standard Operating Procedures for Doxorubicin

### 16.2 Oncology Antineoplastic Hazardous Drug Handling Policy

## 17 References

[Provide the citations for all publications and presentations referenced in the text of this document.]

## 18 Attachments

### 18.1 Appendix I

### 18.2 Sample Collection & Processing

#### 18.2.1 Sample collection and processing (Day -7 Pre-Enrollment):

18.2.1.1 Collect **6-8mL** blood for CBC/Chem (+/- MDR mutation testing if at risk breed\*), ≥3mL urine for standard UA

*18.2.1.1.1 Process as usual per VMTH protocol*

*18.2.1.1.1.1 \*Submit MDR mutation test with Research Sample Request form if performed*

18.2.1.2 Place torn patient sticker on window portion of all sample tubes. Do not cover tube sticker or write patient info on it.

#### 18.2.2 Sample collection and processing (Day 0 Enrollment & Lymphodepletion):

18.2.2.1 Collect 10mL of whole blood in (2) 5mL (K3) EDTA tube for PBMCs

*18.2.2.1.1 Sample will be refrigerated until pick-up*

*18.2.2.1.2 See contact information ([name] lab) below for same-day pick-up. [name] lab should be notified a minimum of 24-hours in advance*

18.2.2.2 Collect 6mL blood for CBC/Chem

*18.2.2.2.1 Process as usual per VMTH protocol and submit with Research Sample Request form.*

18.2.2.3 Place torn patient sticker on window portion of all sample tubes. Do not cover tube sticker or write patient info on it.

*18.2.2.3.1 Submit cytology per VMTH protocol with Research Sample Request form*

## CONFIDENTIAL

### **18.2.3 Sample collection and processing (Days 7, 14, and 35):**

18.2.3.1 Collect 10mL of whole blood in (2) 5mL (K3) EDTA tube for PBMCs

*18.2.3.1.1 Sample will be refrigerated until pick-up*

*18.2.3.1.2 See contact information ([name] lab) below for same-day pick-up. [name] lab should be notified a minimum of 24-hours in advance*

18.2.3.2 Collect 3mL blood for CBC

*18.2.3.2.1 Process as usual per VMTH protocol and submit with Research Sample Request form.*

18.2.3.3 Place torn patient sticker on window portion of all sample tubes. Do not cover tube sticker or write patient info on it.

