#### 3.4 Primary Safety Endpoints

Based on VCOG and known toxicity of doxorubicin. Toxicity will be assessed using client completed forms along with physical exam, temperature, CBC, Chemistry panel, urinalyses.

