## 7 Study Procedures

### 7.1 Schedule of Events

| Procedure                               | Day -7 to -1   | Day 0          | Day 7          | Day 14 | Day 21 | Day 35 | Day 49 | Follow-up q8wks  |
|-----------------------------------------|----------------|----------------|----------------|--------|--------|--------|--------|------------------------------|
| Caregiver informed consent              | X              |                |                |        |        |        |        |                              |
| MDR Test in susc. breed                 | X              |                |                |        |        |        |        |                              |
| Screening echocardiogram                | X              |                |                |        |        |        |        |                              |
| Nebulizer demonstration with saline     | X              |                |                |        |        |        |        |                              |
| Nebulizer sent home for desensitization | X              |                |                |        |        |        |        |                              |
| Physical Examination                    | X              | X              | X              | X      | X      | X      | X      | X                            |
| Quality of Life Form                    | X              | X              | X              | X      | X      | X      | X      | X                            |
| CBC                                     | X  | X              | X              | X      | X      | X      |        |                              |
| Serum biochemistry                      | X  |                | X              |        | X      |        |        |                              |
| Urinalysis                              | X  |                |                |        | X      |        |        |                              |
| PBMCs                                   |                | X              | X              | X      | X      | X      |        |                              |
| Thoracic radiographs                    |                | X  |                |        |        | X      | X      | X                            |
| Doxorubicin administration              |                | X              |                |        |        |        |        |                              |

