- Physical examination and confirmation of eligibility
- Quality of life assessment form
- 11.5 mL blood will be collected for PBMCs and CBC
- Obtain baseline thoracic radiographs (sedation likely required)
- Bloodwork evaluated for adequacy by primary clinician prior to chemotherapy administration
- Doxorubicin @ 30mg/m^2 or 1mg/m^2 IV depending on clinician prescription, both prepared and administered by medical oncology staff
- Patient sent home under owner's care
- Client provided chemosafety information and routine PRN meds

#### 7.2.3 Follow-up – Visit Day 7

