##### Start Inhaled IL-15 Therapy:

- Physical examination
- Quality of life assessment form
- 13 mL of blood obtained for CBC, Chem and PBMC's
- CBC evaluated by trials clinician
  - No minimum cell requirements for IL-15 administration, but if clinically unwell from doxo, may delay
- Inhaled IL-15 (50ug) started in hospital followed by 2 hours monitoring (See XXX section for monitoring details)
- 14 days' supply of IL-15, required PPE, IL-15 Administration Diary sent home with owner

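### Appendix I draws chemistry on Day 0 instead of Day 7; if staff follow it, no chemistry panel falls between doxorubicin and the start of IL-15

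*Protocol*

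**What the plan says.** Three parts of the protocol specify the blood tests.

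- **Schedule of Events (7.1).** In both copies of the table, the row "Serum biochemistry" is marked at screening, Day 7 and Day 21. Days 0, 14, 35 and 49 are blank.
- **Visit text (7.2).** Day 0 (7.2.2): "11.5 mL blood will be collected for PBMCs and CBC". Day 7 (7.2.3): "13 mL of blood obtained for CBC, Chem and PBMC's". This agrees with the schedule.
- **Appendix I (18.2).** Day 0 (18.2.2): "Collect 6mL blood for CBC/Chem", besides 10 mL for PBMCs. Days 7, 14 and 35 share one section (18.2.3): "Collect 3mL blood for CBC", besides 10 mL for PBMCs. Day 21 (18.2.4) asks for CBC and chemistry, as the schedule does.

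Section 7.5 refers the reader to the appendices, and to a separate SOP companion document, for laboratory procedures. On the use of these data, section 3.4 states: "Toxicity will be assessed using client completed forms along with physical exam, temperature, CBC, Chemistry panel, urinalyses". Section 9.1 (Laboratory Value Findings) counts follow-up chemistry values outside the reference range as adverse events. Under section 6.2, doxorubicin is given on Day 0 and IL-15 runs for 14 days from Day 7.

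**The concern.** Appendix I swaps the tests of two visits that fall on either side of doxorubicin. The Day 7 panel is the only one scheduled after doxorubicin and before IL-15 takes effect. A Day 0 panel, by contrast, adds a second baseline to the screening panel, which is itself taken within 7 days of Day 0.

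Toxicity is the secondary objective (2.2) and a secondary endpoint (3.3), and section 1.1 also lists safety among the primary endpoints. With one arm and 10 dogs, the timing of an abnormality within a dog is the main information on when in the sequence it arose. A Day 7 sample that was not drawn cannot be recovered later.

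**Working it through.** No power or error rate enters this point. The check is a visit-by-visit comparison and addition of volumes.

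**Chemistry panels by source**

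| Visit | Schedule 7.1 | Visit text 7.2 | Appendix I |
|---|---|---|---|
| Screening | yes | yes | yes |
| Day 0 | no | no | **yes** |
| Day 7 | yes | yes | **no** |
| Day 14 | no | no | no |
| Day 21 | yes | yes | yes |
| Day 35 | no | no | no |

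Counts per dog:

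- All panels: 3 under the schedule (screening, Days 7 and 21); 3 under Appendix I (screening, Days 0 and 21).
- After doxorubicin: 2 under the schedule; 1 under Appendix I.
- After doxorubicin and by the start of IL-15: 1 under the schedule; 0 under Appendix I.
- First post-doxorubicin panel: Day 7 under the schedule; Day 21 (+/- 3 days) under Appendix I. That is 21 - 7 = 14 days later, at about the end of the 14-day IL-15 course.

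If Appendix I were followed in all 10 dogs, post-doxorubicin panels would fall from 2 x 10 = 20 to 1 x 10 = 10.

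**What this does to the toxicity data.** A chemistry value that is out of range on Day 7 is not seen that day. If it has normalised by Day 21, it is never recorded as an adverse event. If it persists, it is first recorded at Day 21, with no information on whether it preceded IL-15.

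**Blood volumes.** Appendix total = 10 mL for PBMCs + clinical blood.

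| Visit | Visit text (mL) | Appendix I (mL) | Difference (mL) |
|---|---|---|---|
| Day 0 | 11.5 | 10 + 6 = 16 | 4.5 |
| Day 7 | 13 | 10 + 3 = 13 | 0 |
| Day 14 | 11.5 | 10 + 3 = 13 | 1.5 |
| Day 21 | 13 | 10 + 6 = 16 | 3 |
| Day 35 | 11.5 | 10 + 3 = 13 | 1.5 |

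The totals disagree at four of the five visits. At Day 7, the visit that matters here, they agree, so a check of volumes would not reveal the missing chemistry.

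**The case against.** The conflict itself is hard to dispute: Appendix I distinguishes CBC from CBC with chemistry throughout, and its Day 21 entry matches the schedule on tests. The case on the other side concerns consequence and remedy, and much of it stands.

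- **The loss is conditional.** Two copies of the schedule and the visit text agree on Day 7 chemistry, and staff who follow them will draw it. Section 7.5 also cites a companion SOP that is not at hand, so which document governs collection in practice is unknown. A reader might infer that the panel will be lost in all dogs; the documents support only that it would be lost where Appendix I is followed.
- **No chemistry check is made a condition of IL-15.** A reader might infer that IL-15 would start without a planned organ-function review. Section 7.2.3 names only the CBC as evaluated on Day 7, sets no minimum counts, and allows delay if the dog is clinically unwell. Chemistry is drawn, but no text requires its review before the first dose.
- **A Day 7 panel does not separate the two toxicities.** Every dog receives both agents in the same order. The panel dates abnormalities present by Day 7; it cannot assign those arising between Days 7 and 21 to either agent. Section 1.1 frames safety as that of the combination. The Day 7 physical examination, CBC and quality-of-life form are unaffected.
- **Day 0 chemistry may be intended.** Section 7.2.2 has the clinician judge bloodwork before chemotherapy. This may mean the Day 0 CBC, the screening panel, or a Day 0 panel; the text does not say. One cannot conclude that the Day 0 panel should simply be deleted.
- **The volume differences are small.** Dogs must weigh more than 15 kg, so the largest draw is below 16 / 15 = 1.07 mL/kg.

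What remains is that an operative instruction omits a scheduled safety measurement at the one time when it can show the state of the dog between the two agents.

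**Conclusion.** The contradiction is real and worth correcting before further dogs are sampled. Where Appendix I is followed, post-doxorubicin chemistry panels fall from two to one per dog, and those between doxorubicin and IL-15 from one to none, while the total stays at three. Abnormalities at Day 7 go unrecorded at that visit, and changes found at Day 21 cannot be placed before or after the start of IL-15. This weakens the toxicity endpoint. It does not touch the radiographic response endpoint or the sample size of 10.

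The conclusion rests on one assumption: that Appendix I is used as a collection instruction, as section 7.5 indicates. It does not rest on any claim that chemistry gates IL-15, or that a Day 7 panel would by itself attribute toxicity to one agent. The volume disagreements are minor.

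**What to change.** - Reconcile 7.1, 7.2 and 18.2 so that each visit has one test list and one blood volume.
- Take Day 7 out of the CBC-only group in 18.2.3 and give it its own entry (CBC, chemistry and PBMCs), so that the chemistry already scheduled for that visit is drawn.
- Have the sponsor state whether Day 0 chemistry is intended, in view of the pre-chemotherapy bloodwork review in 7.2.2, and write the answer into all three places.
- Check that the companion SOP document cited in 7.5 carries the same lists.

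The cost is a text correction. Day 7 chemistry is already in the schedule, so it adds no test. Section 14.3 says that the study pays for blood sampling after enrolment; it does not itemise chemistry, so cover for the panel is a reasonable inference and not a stated fact. If the sponsor decides to keep Day 0 chemistry as well, that is a fourth panel per dog relative to the schedule, or at most 1 x 10 = 10 further panels.

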### **18.2.4 Sample collection and processing (Day 21 Follow-Up):**

18.2.4.1 Collect 10mL of whole blood in (2) 5mL (K3) EDTA tube for PBMCs

*18.2.4.1.1 Sample will be refrigerated until pick-up*

*18.2.4.1.2 See contact information ([name] lab) below for same-day pick-up. [name] lab should be notified a minimum of 24-hours in advance*

18.2.4.2 Collect 6mL blood for CBC/Chem and  $\geq 3$ mL urine for standard UA

*18.2.4.2.1 Process as usual per VMTH protocol and submit with Research Sample Request form.*

18.2.4.3 Place torn patient sticker on window portion of all sample tubes. Do not cover tube sticker or write patient info on it.

## **Appendix II**

### **SOP07-A Drug Preparation, Handling, and Dispensation of inhaled rhIL-15**

#### **1.0 Purpose:**

The purpose of this standard operating procedure (SOP) is to explain the proper procedures, handling, and dispensation of IL-15

CONFIDENTIAL

This material is the property of the University of California Do not disclose or use except as authorized in writing by the study sponsor

## 2.0 Scope/Responsibility:

These procedures are to be followed by staff responsible for requesting, receiving, and dispensation for client to use the IL-15.

## 3.0 Request, Shipping, Receipt, and Dispensing:

### Request for rhIL-15:

- Sites will be responsible for requesting rhIL-15 shipment from UC Davis.
- To facilitate timely shipment, please email [name] [REDACTED] and [name] [REDACTED] as soon as the surgery date is determined.
- Upon receipt of patient information and anticipated surgery date, UC Davis will notify coordinators/site PI of the planned shipment date.

### Receipt and dispensation of rhIL-15 for nebulization:

- Upon receipt, site is to immediately place IL-15 at 4C.
- Inspection of syringes and Temperature Tracking Device/Card – Please confirm that proper temperature was maintained during shipping and transport. If temperature tracking device is acceptable, please obtain and email a photo of the temperature tracking device to [name] [REDACTED] and [name] [REDACTED]. If concerns, please also send an image and contact [name] or [name] immediately.
- Each site pharmacy will create a label: The script will be printed by the pharmacy and include: **\*Refrigerate\*** place 3mL of prepared drug into the nebulizer well. Administer twice a day over 10-15 minutes or until vapor is no longer seen, as demonstrated for owner, for 14 days.

## 7.0 Reconciliation of study drug:

IL-15 vials will be recorded on the drug accountability log and recorded dose per patient. This will account for the drug used and the drug left over at the end of the study.

## 8.0 Destruction of Study Drug:

Any unused drug will be returned to the participating site and will be held at 4C until the patient is removed from study, at which time unused drug will be returned to UC Davis.

CONFIDENTIAL

## **IL-15 Drug Preparation, Handling, and Dispensation of inhaled rhIL-15**

### **1.0 Purpose:**

The purpose of this standard operating procedure (SOP) is to explain the proper procedures, preparation and dispensation of IL-15

### **2.0 Scope/Responsibility:**

These procedures are to be followed by staff responsible for reconstituting, drawing up and packaging for client to use the IL-15.

### **3.0 Materials:**

- 3x 18g x 1 ½ needle (or similar)
- 1x 10 or 20mL syringe (to remove saline)
- 1x 1mL syringe (to add BSA)
- 1x 3mL syringe (to add IL-15)
- rhIL-15 is stored in -80C freezer
- 9% BSA is stored at -20C freezer (PROVIDED BY UC DAVIS)
- 100mL 0.9% saline bag **stored at 4C**

Volume chart for making up 90mL of IL-15 final working concentrations with 0.1% BSA and 0.9% Saline. rhIL-15 stock = 510ug/mL in solution of 25mM Sodium Phosphate, 500mM Sodium Chloride, pH 7.4. 1mL volume per vial. Stored at -80C

| Actual Dose | Actual IL15 Conc. | Saline Vol. to Discard | 9% BSA to Add | Stock IL-15 (510µg/mL) to Add | Vials of IL-15 to Thaw |
|--------------------|-------------------|-------------------------------|----------------------|--------------------------------------|------------------------|
| 50ug               | 16.7 µg/mL        | 14.0 mL                       | 1.0 mL               | 3.0 mL                               | 3                      |

### **4.0 Procedure:**

#### **IL15 Formulation:**

1. Place 100mL 0.9% saline bag at 4C (if not already)
2. Thaw 1x vial of 9% BSA at room temp
3. Thaw 3 vials of rhIL-15 (1mL of 510µg/mL per vial)
4. Remove 14.0 mL of saline from 100mL saline bag
5. Add 1.0mL of 9% BSA to the saline bag and mix well  
**\*\*\*NOTE: Add BSA and mix BEFORE adding IL-15 to saline bag \*\*\***
6. Add 3.0mL of rhIL-15 stock to saline bag and mix well
7. Fill 30 x 5mL syringes with **exactly 3mL** of IL-15 solution in each.
8. Cap syringes with needleless syringe caps and **store refrigerated at 4C**
9. **Store at 4C until shipment, DO NOT FREEZE**

CONFIDENTIAL

This material is the property of the University of California Do not disclose or use except as authorized in writing by the study sponsor

18.2.5.4

**Appendix III**

**Owner Administration Instructions for inhaled rhIL-15**

**Desensitization and Positive-Reward Training for Inhaled IL-15 Therapy**

It is important to introduce this therapy in a stepwise approach, adding only one “new” thing at a time. Desensitization moves at a different pace for each dog, but it is critical that we match their pace so that we don’t accidentally enforce avoidance behavior. This being said, nebulization is a lot to ask, and some dogs may simply be too anxious to accept this treatment. In addition, if the nosecone is not working, we can try an alternative “bag” approach which is potentially less confining. Ultimately our goal is to train them to rest comfortably and undergo nebulization therapy for around 10-12 minutes twice daily. You obviously know your dog best, but we think the following outlined steps should be useful as you move through this training.

1. Using the cone or mask by itself (no tubing etc.), place the cone over the muzzle for just a second or two followed by a reward treat. Do this several times over the course of the first day gradually increasing the time as tolerated. Avoid having your pet struggle, simply build up the time based on their comfort and always follow with a reward treat and positive reassurance.
2. Find a designated, well ventilated, and cool area within your home that has a power outlet where treatment sessions can take place. Have your pet sit or lay with you in this spot and continue to introduce the cone for increasing periods of time, followed by treat rewards. Of course, belly petting, reassurance and comforting is always encouraged!
3. Now, go ahead and connect the tubing to the nosecone (not attached to the nebulizer), just so they get used to this addition, and continue to practice for longer periods of time.
4. Once your dog is comfortable with the cone and the space, it is time to introduce the nebulizer. This should also be introduced stepwise. First plug the nebulizer in, keep it turned off, but keep it next to you while you are continuing to desensitize to the cone. Once you feel your pet is ready, you can turn the nebulizer on and let it run (so they get used to the noise)
5. The next step is to actually connect the nebulizer to the tubing and cone. This will introduce a stream of air into the nosecone, which will be new for them. Again, move at their pace and continue with positive reinforcement.
6. Once they are comfortable with the cone, the noise, and the airflow; you should add 3 milliliters of saline to the nebulizer cup. This will create the vapor which they will recognize as new but should get used to fairly quickly.
7. Last but not least, during these sessions, your dog will need to get used to your personal protective equipment (PPE)! This will include your gown, gloves, eye protection, and mask. Remember, we just want to introduce one of each of these new things at a time. We would suggest you move in the order of gown, gloves, goggles, and then mask. It may be helpful to have your dog see you put these on.
8. Once your dog has received the 14 days of treatment please remember to collect all the Personal protective equipment, the nebulizer, hose and mask, and any unused drug and supplies and return it to UC Davis at your appointment the following day.
9. **Training video specific for this study:**

CONFIDENTIAL

This material is the property of the University of California Do not disclose or use except as authorized in writing by the study sponsor

- a. <https://ucdavis.box.com/s/oqpdqj9vo5ew4adyyw279u2zhj71oyil>
- 10. You Tube videos if you have any questions regarding your machine:
  - a. <https://www.youtube.com/watch?v=d5AASiAdLiU>
  - b. <https://www.youtube.com/watch?v=rJitnKowVBg>
  - c. <https://www.youtube.com/watch?v=xbj4z4-R7eE>

